## Abstract

Older adults with lower limb fractures often harbor concerns about losing their mobility, fearing a loss of independence. It is vital to develop strategies that foster their active engagement in the rehabilitation process. The present protocol aims to create a care pathway tailored to motivate individuals with lower limb fractures to adhere to rehabilitation. We will develop an observational, cross-sectional, and descriptive study using the Delphi data-gathering approach. Purposive sampling will recruit a panel of healthcare professionals and experts who care for patients with lower limb fractures. Aligned with the Delphi method, a series of iterative rounds will be developed to gather consensus around the motivational strategies used by health professionals in the rehabilitation of people with lower limb fractures. We will employ the Qualtrics platform for data collection and analysis, and a consensus target of 75% has been predetermined. For quantitative data analysis, we will use descriptive statistics encompassing a range of measures, including count, mean, standard deviation, median, minimum, maximum, and range. An inductive thematic analysis procedure will be employed to extract meaningful themes and patterns from qualitative data. The study results are expected to significantly impact clinical practice by creating a specialized care pathway to motivate individuals with lower limb fractures to adhere to rehabilitation. Adopting these explicit standards by professionals will ensure uniform and high-quality care.

## Introduction

1

Bone fractures are a global public health concern, carrying a substantial economic impact on society (1). A bone fracture entails a complete or partial break in the anatomical continuity of bone caused by factors like high-force impact, stress, minor injuries, or specific medical conditions such as osteoporosis, resulting in a loss of mechanical stability (2, 3).

Fractures are not limited by age, affecting individuals of all age groups. However, the specific type and location of fractures differ significantly due to various factors, primarily attributed to individual bone quality and trauma (4). Bone fractures are prevalent and result in a significant financial burden on society due to their high healthcare expenses. Fractures pose a notable public health concern, leading to work absenteeism, decreased productivity, disability, health complications, and considerable healthcare costs. This substantially burdens individuals, families, societies, and healthcare systems (1, 5).

The incidence of fractures is rising (5–7), primarily attributed to the growing occurrence of fragility fractures among the expanding aging population (3). Lower limb fracture incidence globally differs due to factors including age, sex, socioeconomic status, and geography. Although comprehensive data is not available for every country, specific trends emerge (5). In 2019, over 178 million new fractures were reported worldwide, with patella, tibia, fibula, and ankle fractures being the most common, reaching around 32.7 million cases. Lower limb fractures accounted for 72.2 million incidents (5).

Significant progress have been made in medical and surgical approaches to ensure the rapid recovery of patients and alleviate rising healthcare costs (8). Following a lower limb fracture, patients often require physical therapy—a well-established approach in rehabilitating such cases (9) that yields enduring advantages such as enhanced physical function and diminished pain, resulting in an improved quality of life and alleviated healthcare system burdens as patients become empowered to manage their health (10–12). In addition, the rehabilitation team often recommends home exercise programs for clinical rehabilitation or self-managing long-term conditions (13). However, adherence to these programs remains challenging (14), impacting rehabilitation efficacy and potentially leading to the recurrence of injuries or reduced functionality (15).

Increasing adherence to rehabilitation is crucial, especially for older populations, as lower limb fractures can have a significant impact, even when rehabilitation is feasible. Previous studies have shown that older adults who experience a lower limb fracture, fear never regaining their ability to walk again and losing their independence (16–18). This underscores the need to develop strategies that actively motivate these individuals to engage in rehabilitation programs.

Prior studies show exercise self-efficacy correlates positively with initiating and maintaining exercise, especially in planned programs (19–22). However, a complex interplay of factors influences non-adherence to rehabilitation programs. Effective interventions must address a broad range of motivational constructs. According to Bandura’s Social Cognitive Theory, key constructs such as self-efficacy, outcome expectancies, observational learning, and self-regulation play critical roles in behavior change. Self-efficacy, or the belief in one’s ability to perform a specific task, is central to initiating and sustaining rehabilitation activities. Outcome expectancy, the belief that a particular behavior will lead to desired outcomes, further influences motivation (23, 24).

Interventions designed to motivate hold great promise (25–27). They can leverage these constructs by enhancing self-efficacy through mastery experiences (successful completion of tasks), vicarious experiences (observing others succeed), verbal persuasion (encouragement from healthcare providers), and managing physiological and emotional states to reduce anxiety and improve confidence (23, 24). By grounding interventions in Bandura’s theoretical framework, we can more effectively address the multifaceted nature of motivation. However, consensus on how to engage patients for fracture rehabilitation is still uncertain. The lack of guidance and formalized training may have a negative impact not only on patient experience but also on health outcomes. Therefore, this study aims to create a care pathway tailored to motivate individuals with lower limb fractures to adhere to rehabilitation.

## Materials and methods

2

### Study design

2.1

This research will employ an observational, cross-sectional, and descriptive design, utilizing the Delphi method as the data-gathering approach.

The Delphi method is widely recognized for achieving consensus and gathering expert opinions (28). Through a panel of experts, this study seeks to assess the extent of agreement and resolve disagreement on the motivational strategies used by health professionals. The Delphi method is well-suited to the study aims, allowing us to effectively engage numerous geographically dispersed experts cost-efficiently. Through this approach, we aim to develop an evidence-based care pathway that can enhance adherence and optimize recovery for individuals with lower limb fractures.

To ensure the quality of the research protocol report, we will follow the Recommendations for the Conducting and REporting of DElphi Studies (CREDES) (29).

### Research steering group

2.2

A research steering committee will conduct and oversee this research endeavor. Their primary responsibility will involve formulating and disseminating the content for the Delphi rounds. The committee will comprise seasoned researchers with diverse expertise in general practice, geriatrics, nursing, and physiotherapy. Members of the research steering committee will oversee the surveys but not participate in them.

### Participants and recruitment

2.3

The panel members’ experience and expertise will play a crucial role in maintaining the study quality (30). Therefore, we will use a purposive sampling approach to enhance the sample specificity and ensure that the outcomes remain relevant to the research context. This sampling approach allows researchers to select participants with distinct characteristics relevant to exploring data related to the subject of focus (31). We will purposefully select participants with diverse professions and ranges of caregiving experience for patients with lower limb fractures. This will enable the inclusion of participants who can provide diverse lived experiences. The study population includes healthcare professionals, such as nurses, doctors, and physiotherapists.

We will promote the study through various social media platforms such as Facebook, WhatsApp, and LinkedIn. Additionally, our research team will conduct thorough literature searches to identify national and international experts in the field. We will identify essential papers and extend invitations to the respective authors, formally requesting their participation on the panel. These invitations will be sent via email and social media. This approach ensures the formation of a diverse and knowledgeable group.

*Inclusion criteria*
Be a healthcare professional/ researcher;Previous experience in caring for patients with lower limb fractures (2 year minimum);Proficiency in reading and understanding English;Willingness to participate in the study;Declaration of any conflicts of interest.

*Exclusion criteria*
Insufficient experience in caring for patients with lower limb fractures (less than 2 years);Unable to commit to be available for the entire Delphi rounds.

The registration survey will ask participants about their profession and the number of years they have spent caring for others. This will facilitate the sampling process.

Appropriate candidates will be formally invited via email to join the panel, including comprehensive information regarding the study’s objectives, design, and commitment to participate in all Delphi rounds. The email will further encompass a brief online tutorial, lasting approximately 1–2 min, that expands on the overall Delphi process with visual support. This tutorial will aid in offering a clear understanding of the expected process. It will be emphasized that participation will extend over several months, encompassing multiple rounds of inquiries and feedback. At this stage, participants will also be invited to nominate peers interested in participating.

### Data collection instrument

2.4

This study is built upon a prior scoping review (32) undertaken by the research team, which aimed to identify in the literature motivational strategies used by health professionals in the rehabilitation of people with lower limb fractures.

In light of the insights gained from the scoping review, the next phase of our research will involve developing a Delphi survey. This questionnaire will be constructed based on the motivational strategies that emerged from the scoping review (Table 1).

**Table 1 tab1:** Motivational strategies.

Strategies	Interventions
Therapeutic alliance	A thorough interview on admission.
	Develop a trusting and motivating relationship.
	Feelings of mutuality and respect in the alliance.
	Face-to-face counseling sessions.
Health literacy	Educate patients in rehabilitation exercise, complications, disease, and the benefits of exercise.
	Provide information leaflets/booklets.
	Cueing with posters describing the exercises.
Set achievable goals	Identify patients’ abilities and needs.
	Conferrer with patients to develop functional exercise goals at different stages of rehabilitation.
	Physical activity diary.
	Calendar of daily exercise activities.
Personalize the rehabilitation program	Develop an individually tailored exercise program.
	Tailor the instruction and program to make the task understandable.
Manage unpleasant sensations	Identifying challenges of postoperative rehabilitation through discussion.
	Use prescribed medications or heat/ice treatment to relieve or decrease pain.
Sharing cases	Share previous success stories to build confidence and motivate patients.
Problem-solving method	Identify obstacles to participating in the rehabilitation program.
	Use the problem-solving method to address perceived obstacles to participation in rehabilitation programs.
Persuasion	Describe the benefits of physical activities.
	Behavioral contract.
	Regular contact with patients via phone.
Encouragement and compliment	Assert that participants can self-manage.
	Provide positive verbal feedback upon their efforts.
	Give verbal encouragement and compliment.
	Motivation interviewing.
	Reinforce participants’ past and present successes or accomplishments.
	Family involvement.
	Digital activity coaching system.
Avoid negative emotional stimulation	Assess patients’ expressions of anxiety and depression.
Help to seek support	Telephone-assisted counseling.
	Identify individual barriers and resources for performing the exercise plan.
	Provide strategies for dealing with the identified barriers and coping in the future.

Critics have raised concerns about the limitations of traditional Delphi study designs in facilitating experts’ detailed explanations of their viewpoints (33). The present study will adopt a modified Delphi study design, as participants can elaborate on their opinions. In the initial round, they will also be prompted to identify any supplementary strategies they are familiar with or employ in their professional practice.

The survey will be developed using the Qualtrics platform (Qualtrics, Provo, UT, USA). Before it is applied, a pre-test will be conducted to assess comprehension and adequate functioning of the survey.

Each item will be evaluated using the Grading of Recommendations Assessment, Development, and Evaluation (GRADE) scale, which ranges from 1 to 9. The scale determines the significance of each item for inclusion: a score of 1–3 indicates it is not important for inclusion; 4–6 signifies importance, but not criticality; and 7–9 suggests it is critical for inclusion (34). The inclusion/exclusion criteria will consider items that achieve a ‘not important for inclusion’ or ‘critical-to-include’ rating in more than 75% of the responses. Given the absence of a clearly defined consensus criterion, we found this threshold and approach to be pragmatic and reasonable for consensus establishment, as they represents the perspective of three-quarters of the experts.

Items lacking consensus will progress to the subsequent round. Suppose there is no significant answer change about a specific item, characterized by a change of less than 20%. In that case, researchers will consider that consensus cannot be attained for that item and, therefore, exclude the item from subsequent rounds.

### Rounds

2.5

We will conduct a sequence of online survey rounds (Figure 1). Participants will receive exclusive links to each round via email on the first day. Each round is expected to take approximately 25–30 min to complete and will be open for 4 weeks. A minimum of 2 weeks will be allocated for result analysis between successive rounds. To ensure retention, participants will receive up to four email reminders for each round, encouraging completion before its closure, unless they choose to withdrawal from the study.

**Figure 1 fig1:**
[figure not shown]
Flow chart to illustrate the stages of the Delphi process.

A total of 11 strategies have been identified for panel members to consider in Round 1 (Table 1). In Round 1, participants will access the online survey containing contextual details, survey instructions, and question-specific help resources. Demographic information will be collected, including age, sex, occupation, academic degree, years of work experience, and years of experience caring for patients with lower limb fractures. During this phase, participants will review the provided strategies and interventions, determining whether they wish to offer additional outcomes for consideration. Each survey item will feature a comment box where participants can suggest rephrasing, identify any omissions, propose new items, and offer reasons behind their choices.

The answers collected during each round will be aggregated and subjected to analysis. The summarized overview of data will be shared anonymously with participants as part of the introductory materials for the second round. This deliberate anonymity serves the dual purpose of fostering candid responses, as experts can contribute without being influenced by the input of their peers. Additionally, it empowers experts with the liberty to revise their initial responses if deemed suitable without any awareness on the part of their fellow experts. This confidentiality measure contributes to the integrity of the Delphi process and encourages genuine, uninfluenced participation.

In Round 2 participants will be asked to rate the appropriateness of the strategies as one that could be employed in patients with lower limb fractures. Following their ratings, participants will be asked to explain the reasons underlying their assessments.

In Round 3, the panel will have the chance to revisit their Round 2 responses for items where consensus is still pending. This opportunity arises from feedback on the group’s Round 2 responses. The overall process remains consistent with Round 2, albeit with a focus shift. Participants will be tasked with assessing the suitability of the interventions for potential implementation in patients with lower limb fractures. A fourth round will follow if consensus needs to be met after Round 3. During this round, panel members can reassess their Round 3 responses for items lacking consensus.

Like the previous round, participants will provide ratings for the appropriateness of these interventions. Following the rating process, participants will be encouraged to provide insights into the reasoning behind their evaluations.

Participants must respond to all rounds to successfully conclude the Delphi process. Consequently, individuals who did not participate in Round 2 will not be invited to participate in Round 3.

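### The consensus bands measure importance for inclusion, but the rounds are described as rating appropriateness or suitability, and Round 3 also changes what is rated

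*Protocol article*

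**What the plan says.** **Scale and rule (section 2.4, Data collection instrument).** There is one response scale: "Each item will be evaluated using the Grading of Recommendations Assessment, Development, and Evaluation (GRADE) scale, which ranges from 1 to 9". Its meaning is given directly: "The scale determines the significance of each item for inclusion: a score of 1–3 indicates it is not important for inclusion". The upper bands follow: "4–6 signifies importance, but not criticality; and 7–9 suggests it is critical for inclusion". Inclusion or exclusion is decided for "items that achieve a ‘not important for inclusion’ or ‘critical-to-include’ rating in more than 75% of the responses". Items without consensus go to the next round. An item whose answers change by less than 20% is treated as unable to reach consensus and is dropped.

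**Rating tasks (section 2.5, Rounds).**
- Round 1 is described as review and comment, with suggestions for additions.
- In Round 2, "participants will be asked to rate the appropriateness of the strategies as one that could be employed" in these patients.
- In Round 3, panellists may revisit Round 2 answers on undecided items. The process is said to be the same as in Round 2 but with a changed focus, and the task is "assessing the suitability of the interventions for potential implementation".
- Round 4 is introduced as being like the round before it: "participants will provide ratings for the appropriateness of these interventions".

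**The concern.** Whether something could be used is a question of permissibility. Whether it is critical to include is a question of priority. The middle band of the scale exists to separate useful items from essential ones. An information leaflet, one of the interventions in Table 1, could reasonably earn an 8 as something one might use and a 5 as something the pathway must contain. The decision rule would count that 8 as a vote for critical.

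Table 1 comes from the team's scoping review of strategies that health professionals use. A question about possible use therefore plausibly draws higher scores than one about criticality. The rule decides what goes into the pathway, and the Discussion expects the pathway to set explicit standards for practice.

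The second issue is the move from strategies in Round 2 to interventions in Round 3. The rule on changes below 20% needs the same item in two successive rounds. If the rated object changes, an apparent change or lack of change in answers does not measure stability of opinion.

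**Working it through.** **1. Construct, section against section.**

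| Element | Where | What is judged | Rated object |
|---|---|---|---|
| 1–9 bands | 2.4 | importance for inclusion | each item |
| >75% rule | 2.4 | not important, or critical | each item |
| Round 2 | 2.5 | appropriateness for possible use | strategies |
| Round 3 | 2.5 | suitability for possible use | interventions |
| Round 4 | 2.5 | appropriateness | interventions |

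No round description mentions importance or criticality for inclusion. No appropriateness scale is given, and no rule converts appropriateness into the 2.4 bands.

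**2. Rated object.** Table 1 lists 11 strategies (also stated in section 2.5). Counting its rows gives 4 + 3 + 4 + 2 + 2 + 1 + 2 + 3 + 7 + 1 + 3 = 32 interventions. A strategy covers between 1 and 7 interventions, so a Round 2 strategy rating has no single Round 3 counterpart. The comparison between Rounds 2 and 3 is undefined as described. The comparison between Rounds 3 and 4, both on interventions, is not affected.

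**3. Sensitivity of the >75% rule (illustration only).** The document gives no expected score distribution, so the probabilities below are assumptions.

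The panel sizes come from section 2.6: at least 95 experts and 25% dropout between rounds. The 95 reproduces as 30/0.75⁴ = 94.8, rounded up to 95. The target of 30 and the four losses are inferred, not stated. Successive losses give 95 × 0.75 ≈ 71, 95 × 0.75² ≈ 53 and 95 × 0.75³ ≈ 40.

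More than 75% requires m = ⌊0.75n⌋ + 1 scores of 7–9: 54 of 71, 40 of 53, 31 of 40. If panellists answer independently and each scores 7–9 with probability p, the chance of passing is P(X ≥ m) with X ~ Binomial(n, p):

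| p | n = 71 | n = 53 | n = 40 |
|---|---|---|---|
| 0.60 | 0.003 | 0.014 | 0.016 |
| 0.70 | 0.163 | 0.239 | 0.196 |
| 0.75 | 0.482 | 0.542 | 0.440 |
| 0.80 | 0.837 | 0.841 | 0.732 |
| 0.85 | 0.984 | 0.978 | 0.933 |
| 0.90 | 1.000 | 0.999 | 0.995 |

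If the wording of the question moved p from 0.70 to 0.85, an item that would usually fail would usually pass. If p were already 0.90, or stayed at 0.60 or below, a small shift would change little. The table shows how sensitive the rule is. It does not show that such a shift will occur.

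**The case against.** The strongest reply is that section 2.4 fixes the instrument and section 2.5 only narrates the flow in looser words. The GRADE scale applies to every item and is the only scale in the document. If panellists see its anchors on screen, a 7–9 does mean critical. The article paraphrases the tasks and does not reproduce the survey questions, and a pre-test for comprehension is planned. This stands as a possibility, so the document does not show that the survey itself is wrong. It does not remove the conflict: the stated task and the stated bands differ, and importance anchors under an appropriateness question would still leave panellists to choose which to answer.

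Three stronger readings are tempting and are not supported.
- **A different question in every round.** Appropriateness appears in both Round 2 and Round 4, Round 4 is said to be like Round 3, and Round 3 is said to follow the Round 2 process. Suitability looks like a synonym. The firm change between Rounds 2 and 3 is the rated object.
- **Nearly every item ending up critical.** The document holds no data on how panellists will score, and they may add items of their own.
- **The change rule spoiled by rewording.** If the two words are synonyms, rewording is not the cause; the shift from strategies to interventions is.

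**Conclusion.** The point holds as a conflict between two stated parts of the protocol, not as an omission. Followed as written, the rule reads answers about possible use as votes on criticality, and items judged usable but not essential could be included. The mismatch concerns every rating round that section 2.5 describes. Its effect on the final item list cannot be sized from the document; the probabilities in the table are assumptions and serve only to show that a moderate shift in scoring near the threshold can reverse a decision.

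The change of rated object between Rounds 2 and 3 is a separate and firmer problem for the rule on changes below 20%, and harmonising the question alone would not cure it. Both should be settled before launch, because ratings collected under an unclear question cannot be reinterpreted afterwards.

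**What to change.** Reconcile sections 2.4 and 2.5:

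1. Use one question in every rating round that matches the bands, for example: How important is it to include this item in the motivational care pathway? Show the three band labels beside it.
2. If appropriateness is also of interest, ask it separately and keep it outside the consensus rule.
3. State for each round whether strategies, interventions or both are rated, and which Round 2 answers are reopened in Round 3.
4. Apply the rule on changes below 20% only to the same item rated with the same question in successive rounds.

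Before launch this costs edits to the survey wording and to the two sections. It needs no additional panellists or rounds, unless a separate appropriateness question is kept, which would lengthen the survey.
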